#### Online diet and physical activity diary

The Australian Biggest Loser Club online food and exercise diary is powered by the database (International Food and Exercise Database). This database holds the information on over 70,000 foods including 20,000 Australian foods, 250,000 food portions, 5000 meals and recipes, and 1000 exercises. It is derived from a combination of methods including: 1) nutrition information from branded products collected by SP Health; 2) recipes to derive commonly eaten foods developed by an Accredited Practising Dietitian; and 3) sources such as the Australian food database (NUTTAB 2006, Canberra). The METs of exercises have been obtained predominantly from the Ainsworth [19,20] compendium of activities, and all exercise instructions have been compiled by SP Health.

#### Indicators of change in Health Status and Quality of Life

**Blood pressure and resting heart rate: **systolic blood pressure, diastolic blood pressure and heart rate were measured using an automated blood pressure monitor (NISSEI/DS-105E digital electronic blood pressure monitor (Nihon Seimitsu Sokki Co. Ltd., Gunma, Japan) under standardized conditions. Subjects were seated for five minutes before the first blood pressure measurement and a rest period of two minutes between measures. Blood pressure was measured three times. Further measurements were taken if the blood pressure or resting heart rate values fell outside of the acceptable ranges i.e. systolic within 10 mmHg, diastolic within 10 mmHg (preferably 5 mmHg) and resting heart rate within 5 bpm. The mean of the two closest systolic pressures and the diastolic pressure paired to them will be reported. The mean of the two lowest resting pulse pressures will be used.

**Blood sample biomarkers: **blood samples were collected after an overnight fast and analysed using standard automated techniques at a single National Association of Testing Authorities accredited pathology service. The samples were analysed for lipids (Total Cholesterol, Low Density Lipoprotein (LDL) and High Density Lipoprotein (HDL) cholesterol, and triglycerides), thyroid function and liver function, C-reactive protein, glucose and insulin. Additional samples have been stored for future analysis of additional biomarkers.

**Quality of Life: **SF-36, version 2.0 (QualityMetric Incorporated, Lincoln, RI, USA) is a multi-purpose, generic short-form health survey consisting of 36 questions using an 8-scale profile of functional health and well-being scores and psychometrically-based physical and mental health summary measures and scored according to standardised procedures [21]. It has been used widely in surveys of general populations and in differentiating the health benefits produced by a range of different treatments.

#### Use of Internet features and satisfaction with weight loss program

A process evaluation questionnaire was developed from a previous study [22] to assess the use of website features and satisfaction with the web based program, and completed by participants after 3, 6 and 18-months. Objective measurement of participants' use of the website features (e.g. log-ins to specific program features, diary entries, post to bulletin boards) was collected and stored by SP Health Pty Ltd throughout Phase 1 and Phase 2.

#### Timelines for Programs

Baseline assessments occurred in one session and participants in the two intervention groups were able to log on and commence the programs immediately after this initial assessment. This session was conducted early in the morning and participants were offered breakfast following the blood collection, anthropometric and blood pressure assessments. Participants repeated these assessments at 3, 6, and 18 months with the control group having their post-intervention assessments at 9 and 21 months (due to their 3 months wait-list period). To maximize adherence to these sessions, participants were asked to book into an assessment time that suits them using the online scheduling system, Doodle http://doodle.com or alternatively via a telephone call. In addition, for participants difficult to contact other methods were employed such as text messaging and mailing letters. A contribution towards parking and travel costs of $AU10 was given to those attending assessment sessions.

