### Randomization

Once written consent was obtained and baseline assessments completed participants were randomly allocated to one of the three Phase 1 groups (Figure 1) using a stratified randomized block design. Participants were stratified by gender and category of body mass index (25 to <30; ≥30 to <35 or ≥35 to 40) using blocks of variable length (either 3 or 6). Subjects received the next envelope in the sequence based on their stratified BMI and gender group. Envelopes were prepared ahead of time, sealed and distributed by a researcher not involved in data collection. Subjects were asked to not open their allocation envelope until they returned home. Subjects were re-randomized in the same way at the end of the weight loss phase to one of the two maintenance arms.

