#### Physical activity

**International Physical Activity Questionnaire **(short form): data from this questionnaire was used to estimate total MET-minutes/week and to classify participants into either high, medium or low physical activity categories according to the IPAQ Scoring Protocol [18].

**Pedometers: **physical activity was objectively measured using pedometers (Yamax SW700; Yamax Corporation, Kumamoto City, Japan). At baseline, participants were instructed on how to attach the pedometers (at the waist on the right hand side) and asked to remove the pedometers only when sleeping, when the pedometer might get wet (e.g. swimming, showering) or during contact sports. Participants were asked to wear pedometers for seven consecutive days and keep to their normal routine. At the end of the day participants were instructed to record their steps on a pedometer record sheet and reset their pedometers to zero. Participants were instructed to record if they did an activity like cycling, swimming, contact sports or another activity that did not involve stepping and include details (type of activity and duration), or if they forgot to wear their pedometer for an amount of time. Participants will be included in all analyses if they completed at least four weekdays of pedometer monitoring. The average of existing days will be imputed for participants who have included at least four days of data.

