### Data analysis

Analysis will be on an intention-to-treat basis. Analysis of covariance will be used to test for differences in weight loss between groups at 3 months. The model will be fitted using linear regression with weight at 3 months as the outcome variable, treatment group as the predictor variable of interest and weight at baseline included as a covariate. Other independent variables included in the model will be: gender, kilojoule intake at baseline and physical activity at baseline. Differences in weight loss between groups in the weight maintenance phase will be analysed using generalised linear mixed models (GLMM). The outcome in the model will be the individual's weight at the post treatment assessments, the main predictor of interest will be treatment group and baseline weight will be included as a covariate. Other independent variables included in the model will be: time, gender, kilojoule intake at baseline and physical activity at baseline.

Statistical significance of the primary efficacy analysis (at three months and 18 months) will be based on Hochberg's multiple testing procedure with the family wise error rate for each time point held at 2.5%. All secondary hypothesis tests will be performed using a 2-sided 5% significance level. In addition, linear regression and GLMM will be used to describe relationships among the various dependent and independent variables.

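### The baseline pedometer week appears to follow allocation, which can bias the 3-month model if steps are its activity covariate; separately, the pedometer validity rule read literally conflicts with intention-to-treat

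*Protocol article*

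**What the plan says.** Four sections of the protocol article bear on this.

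- **Randomization** puts allocation after baseline: "Once written consent was obtained and baseline assessments completed participants were randomly allocated to one of the three Phase 1 groups". It adds: "Subjects were asked to not open their allocation envelope until they returned home".
- **Timelines for Programs** describes baseline as one session, after which "participants in the two intervention groups were able to log on and commence the programs immediately after this initial assessment".
- **Physical activity** describes two instruments, the IPAQ short form and a pedometer. For the pedometer: "At baseline, participants were instructed on how to attach the pedometers", and "Participants were asked to wear pedometers for seven consecutive days and keep to their normal routine". It then sets a validity rule: "Participants will be included in all analyses if they completed at least four weekdays of pedometer monitoring". The next sentence, on imputation, uses four days of data, with no mention of weekdays.
- **Data analysis** opens with "Analysis will be on an intention-to-treat basis". Both the 3-month linear regression and the maintenance-phase mixed model include physical activity at baseline as a covariate. Neither says which instrument supplies it.

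**The concern.** A seven-day step record cannot be finished within one session. If wear starts from the instruction given there, and the participant takes the envelope home and may log on at once, the week labelled baseline is worn with the allocation known. In Basic and Enhanced it can also be the first programme week, and both programmes supply an activity plan and an exercise diary. Wait-list participants have no website access, so their week is untreated.

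Two things follow. A step count that treatment can move is not a safe covariate for the 3-month comparison, nor a safe starting point for change in steps: an immediate and lasting increase would look like no change. Separately, a rule that ties inclusion in all analyses to pedometer compliance would, taken at its word, remove randomised participants for something that happens after randomisation.

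**Working it through.** **1. Timing.** There are two ways to read the sections together.

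- *The pedometer week counts as a baseline assessment, and Randomization is taken literally.* Allocation then comes at least seven days after the pedometer is handed out. That does not fit a one-session baseline with access to the programme straight afterwards.
- *The pedometer week is not part of what was completed before allocation.* The session and the immediate start then fit together, and the step week falls after allocation.

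The second reading reconciles more of the text, but no section states it. The first moves the conflict elsewhere and does not remove it.

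**2. Which model is exposed.**

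- *3-month model:* exposed only if the covariate is pedometer steps and the week followed allocation. An IPAQ score completed in the session precedes opening of the envelope.
- *Maintenance model:* not exposed. M1 versus M2 rests on a second randomisation after 12 or 24 weeks of weight loss. Steps recorded at study entry precede it, so they are a legitimate covariate there.

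**3. Size of the possible bias at 3 months.** The documents give no first-week uplift and no slope of weight on steps, so both are assumed. Let g be the slope of 3-month weight on steps (kg per 1000 steps, given the other terms) and s the first-week difference in steps per day between arms. Adjusting for steps moves the estimated effect by −g × s/1000. A simulation with 200,000 participants and a true total effect of −2.0 kg gave:

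| s (steps/day) | g (kg per 1000) | −g × s/1000 (kg) | Estimate without steps | Estimate with steps |
|---|---|---|---|---|
| 0 | −0.2 | 0.0 | −2.00 | −2.00 |
| 0 | −0.5 | 0.0 | −1.99 | −1.99 |
| 500 | −0.2 | 0.1 | −1.98 | −1.88 |
| 500 | −0.5 | 0.25 | −2.02 | −1.75 |
| 1000 | −0.2 | 0.2 | −1.99 | −1.79 |
| 1000 | −0.5 | 0.5 | −2.01 | −1.52 |
| 2000 | −0.2 | 0.4 | −2.00 | −1.61 |
| 2000 | −0.5 | 1.0 | −1.98 | −0.99 |

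The loss runs from 0 to 1.0 kg, towards no difference when uplift raises steps and more steps go with lower weight. For Basic versus Enhanced, s is the difference between their uplifts. Both arms receive activity plans, and the documents give no basis for a value.

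**4. The two thresholds.** Seven consecutive days hold five weekdays and two weekend days. Four recorded days that include any weekend day contain at most three weekdays; five that include both weekend days contain three. Such participants meet the four-day rule but not the four-weekday rule. Of the C(7,4) = 35 ways to record exactly four days, only C(5,4) = 5 use four weekdays. With six recorded days both rules are always met.

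**5. What exclusion would cost in power.** The plan's own figure comes first. For a difference of 1.5 kg/m², SD 1.5, two-sided 0.05 and 90% power, n = 2 × (1.960 + 1.282)² × (1.5/1.5)² = 21.0, or 22 per group (23 with the t distribution). This is close to the stated 24 per sex, so 48 looks like 2 × 24. Power is Φ(√(n/2) − 1.96). If the rule dropped an assumed 10%, 20% or 30%:

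| Dropped | 24 per group | 48 per group |
|---|---|---|
| 0% | 93.4% | 99.8% |
| 10% | 90.8% | 99.6% |
| 20% | 87.3% | 99.2% |
| 30% | 82.6% | 98.4% |

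Power is not the main worry. Selection after randomisation is.

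**The case against.** The strongest reply is that the timing is an inference. Randomization says baseline assessments came first, and Timelines for Programs lists blood collection, anthropometry and blood pressure in the session without mentioning pedometers. Participants were also told to carry on as usual that week. This stands in part: a reader might infer that baseline activity *is* affected by treatment, and the documents show only that it *can* be.

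A reader might also infer that both primary models are compromised. They are not, because study-entry steps precede the maintenance randomisation. Nor is the 3-month model exposed if the covariate is IPAQ, which the article describes first and which yields a weekly total. Leaving the instrument unnamed is detail an article may leave to a fuller document. It matters here only because one of the two candidates may be a post-allocation measure.

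The validity rule sits in the pedometer paragraph and was probably meant for pedometer analyses, and it does not say *only* if. That is fair as to intent. The words still reach all analyses, and they sit beside an unqualified intention-to-treat statement.

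Finally, the article specifies no analysis of change in steps, so harm there depends on one being done.

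**Conclusion.** The concern holds in a limited form. The sections conflict on when the baseline step week falls, and the reading that fits most of the text puts it after allocation. If steps are the activity covariate, the 3-month active versus wait-list difference could be attenuated by 0.1 to 1.0 kg with an assumed uplift of 500 to 2000 steps a day and slope of 0.2 to 0.5 kg per 1000 steps. It is unaffected if there is no uplift or if IPAQ is used. The maintenance comparison is not affected.

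A reader might be tempted to express the loss as a share of the planned effect, by converting 1.5 kg/m² to about 4.3 kg (1.5 × 1.70² = 4.34). The documents do not support that. The height is assumed, and the 1.5 kg/m² belongs to a sample size stated for the maintenance groups at 18 months, not to active versus wait-list at 3 months.

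The inclusion rule needs no timing inference: as worded it conflicts with intention-to-treat, and its threshold differs from that of the imputation sentence. The point should be corrected because the remedy is nearly free, not because a bias has been shown.

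**What to change.** 1. In Data analysis, name the IPAQ score completed at the baseline session as the activity covariate in the 3-month model, and confirm that it was completed before the envelope was opened.
2. In Physical activity, restrict the validity rule to pedometer outcomes, choose one threshold for inclusion and imputation, and state that all randomised participants stay in the weight and BMI analyses whatever their pedometer data.
3. Reconcile Randomization, Physical activity and Timelines for Programs by stating when the baseline step week fell relative to allocation and first log-on. If it followed allocation, compare follow-up steps between arms without adjusting for that week or subtracting it.

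Baseline and first allocation are described in the past tense, so these are changes to analysis and reporting only. The cost is wording, plus some lost precision for step comparisons made without a baseline value.

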### Data analysis

Analysis will be on an intention-to-treat basis. Analysis of covariance will be used to test for differences in weight loss between groups at 3 months. The model will be fitted using linear regression with weight at 3 months as the outcome variable, treatment group as the predictor variable of interest and weight at baseline included as a covariate. Other independent variables included in the model will be: gender, kilojoule intake at baseline and physical activity at baseline. Differences in weight loss between groups in the weight maintenance phase will be analysed using generalised linear mixed models (GLMM). The outcome in the model will be the individual's weight at the post treatment assessments, the main predictor of interest will be treatment group and baseline weight will be included as a covariate. Other independent variables included in the model will be: time, gender, kilojoule intake at baseline and physical activity at baseline.

Statistical significance of the primary efficacy analysis (at three months and 18 months) will be based on Hochberg's multiple testing procedure with the family wise error rate for each time point held at 2.5%. All secondary hypothesis tests will be performed using a 2-sided 5% significance level. In addition, linear regression and GLMM will be used to describe relationships among the various dependent and independent variables.

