**Methods/Design:**

Overweight and obese adult males and females were stratified by gender and BMI and randomly assigned to one of three groups for 12-weeks: waitlist control, or basic or enhanced online weight-loss. Control participants were re-randomized to the two weight loss groups at the end of the 12-week period. The basic and enhanced group participants had an option to continue or repeat the 12-week program. If the weight loss goal was achieved at the end of 12, otherwise on completion of 24 weeks of weight loss, participants were re-randomized to one of two online maintenance programs (maintenance basic or maintenance enhanced), until 18 months from commencing the weight loss program. Assessments took place at baseline, three, six, and 18 months after commencing the initial weight loss intervention with control participants repeating the initial assessment after three month of waiting. The primary outcome is body mass index (BMI). Other outcomes include weight, waist circumference, blood pressure, plasma markers of cardiovascular disease risk, dietary intake, eating behaviours, physical activity and quality of life.

Both the weight loss and maintenance of lost weight programs were based on social cognitive theory with participants advised to set goals, self-monitor weight, dietary intake and physical activity levels. The enhanced weight loss and maintenance programs provided additional personalized, system-generated feedback on progress and use of the program. Details of the methodological aspects of recruitment, inclusion criteria, randomization, intervention programs, assessments and statistical analyses are described.

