### Sample size

Based on having 90% power to detect a significant difference in BMI between weight loss groups of 1.5 kg/m^2^, assuming the SD of BMI is 1.5 and using a two-sided significance level of 0.05, a sample size of 48 participants (24 males and 24 females) is needed for each maintenance group at 18 months. This sample size is within the range of other web-based weight loss intervention studies [13].

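### BMI is the declared and powered primary outcome, but both efficacy models in the plan are written for body weight, so no analysis of BMI is specified

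*Protocol article*

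**What the plan says.** **Abstract, Methods/Design.** The primary outcome is named: "The primary outcome is body mass index (BMI"). The next sentence gives weight a lower rank: "Other outcomes include weight, waist circumference, blood pressure", followed by further measures.

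**Sample size.** The calculation is in BMI units: "Based on having 90% power to detect a significant difference in BMI between weight loss groups of 1.5 kg/m^2". The spread is given in the same units ("assuming the SD of BMI is 1.5"). The test is two-sided at the 5% level. The result is 48 participants per maintenance group, 24 of each sex.

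**Data analysis.** Two efficacy models are written out.
- At 3 months, an analysis of covariance: "The model will be fitted using linear regression with weight at 3 months as the outcome variable". Baseline weight is a covariate, with gender, baseline kilojoule intake and baseline physical activity.
- In the maintenance phase, a generalised linear mixed model. Its outcome is weight at the post-treatment assessments, its covariates include baseline weight, and time is added.

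The same section holds the primary efficacy analysis at 3 and 18 months to Hochberg's procedure, with a family-wise error rate of 2.5% per time point. Secondary tests use a two-sided 5% level. The Hochberg sentence names no outcome. A closing sentence on regression and mixed models is descriptive and names none either.

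**Anthropometry.** Height and weight are both measured, and BMI is calculated from them.

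**The concern.** The document ranks BMI first and weight among the rest, sizes the trial on BMI, and then models only weight. Three consequences follow.

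1. **The significance level for weight is undefined.** By the abstract, weight is secondary and is tested at 5%. By the models under Data analysis, it looks like the primary analysis and would fall under the 2.5% rule.
2. **The choice of outcome is left open.** Both measures come from the same visits. A report could present either as primary and cite a section of the protocol in support, after both results are known.
3. **The planned difference does not carry over.** The sample size gives no target difference or SD in kg, so a weight estimate cannot be set against the difference the trial was built to detect.

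This is not a detail that a condensed article leaves to a fuller plan. The article does state its models, covariates and multiplicity rule, and the outcome it states differs from the one it declares.

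**Working it through.** **Step 1: the passages side by side.**

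| Section | Outcome used | Role |
|---|---|---|
| Abstract, Methods/Design | BMI | primary |
| Abstract, Methods/Design | weight | other outcome |
| Sample size | BMI, 1.5 kg/m², SD 1.5 | basis of the calculation |
| Data analysis, 3-month model | weight, adjusted for baseline weight | efficacy model |
| Data analysis, maintenance model | weight, adjusted for baseline weight | efficacy model |
| Data analysis, Hochberg sentence | not named | primary test rule |

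No row gives a model with BMI as its outcome.

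**Step 2: the plan's own sample size.** With difference 1.5, SD 1.5, two-sided alpha 0.05 and 90% power:

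n per group = 2 × (1.960 + 1.282)² × (1.5/1.5)² = 21.01, so 22. The t-test version gives 22.02, so 23.

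The stated 24 per sex per group is within two of this, so 48 fits as two sex-specific calculations. Pooled over sex, 48 per group gives 99.8% power at alpha 0.05 and 99.6% at 0.025 (normal approximation). The figure is therefore a BMI figure throughout.

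**Step 3: the difference in kg.** Since BMI = weight/height², a difference of 1.5 kg/m² equals 1.5 × height² kg. The heights below are assumptions, as the document gives none.
- 1.60 m: 1.5 × 2.56 = 3.84 kg
- 1.70 m: 1.5 × 2.89 = 4.34 kg
- 1.80 m: 1.5 × 3.24 = 4.86 kg

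The ratio of the last to the first is 4.86/3.84 = 1.27. Height is not in either model, and the trial recruits both sexes.

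**Step 4: the significance level.** Hochberg's procedure at a family-wise rate of 2.5% never rejects a p-value above 0.025. A weight p-value of 0.04 would be significant as a secondary result (0.04 < 0.05) and not significant as a primary one (0.04 > 0.025).

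**Step 5: how often the two tests would differ.** Simulated trials had 48 per arm, baseline BMI uniform from 25 to 40 and mean heights of 1.77 m (men) and 1.64 m (women), with within-sex SDs of about 7 and 6.5 cm. The 1.5 kg/m² was read as the residual SD, and alpha was 0.025. Each outcome was analysed with its own baseline value and gender as covariates, over 3,000 trials per setting.

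| True BMI difference | Trials where BMI and weight disagree on significance |
|---|---|
| 0 | 0.8% |
| 0.8 | 3.8% |
| 1.0 | 3.0% |
| 1.5 (planned) | 0.3% |

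At 1.5, power was 99.5% for both. With no true difference, the rejection rate was 2.7% for BMI and 2.6% for weight, against a nominal 2.5%. A second set-up, with normally distributed baseline BMI and alpha 0.05, gave power of 90.2% (BMI) and 89.3% (weight) at 1.0 kg/m², with agreement in about 98% of trials.

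**The case against.** The strongest reply is that little is at stake numerically. Adult height hardly changes over 18 months, so weight is BMI times a fixed personal constant. The simulations bear this out. That stands, and it rules out two stronger readings.

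- A reader might infer that the primary outcome is never tested, or that the primary analysis is definitely an analysis of a secondary outcome. The documents do not establish this. The Hochberg sentence names no outcome. It could refer to the abstract's primary outcome, with the weight models shown as the form of analysis. What the text supports is that no model for BMI is written.
- A reader might infer that power or type I error is damaged. The figures above show no material loss of either.

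A reader might also object that the BMI stratification factor ("Participants were stratified by gender and category of body mass index") is missing from the models. This adds little. Gender is in both models, and gender with baseline weight carries much of the information in the BMI stratum.

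It can fairly be said, too, that the stated aims concern weight loss and its maintenance, so weight may be what the investigators meant. The document does not show which statement is the slip. That is a reason to offer two remedies, not a reason to leave the conflict in place.

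**Conclusion.** The point holds as a contradiction inside the protocol article: the declared and powered outcome is BMI, the modelled outcome is weight, and no analysis of BMI is specified. The harm lies in the definition of the primary analysis: which outcome is held to 2.5%, which result counts as primary, and what difference in kg was planned for. The conclusion from the text needs no assumption. The kg conversions depend on assumed heights. The disagreement rates depend on assumed heights, an assumed baseline BMI distribution and reading the SD of 1.5 as residual. Even though the two tests would usually agree, the conflict should be settled, because it cannot be settled credibly once both results are known.

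**What to change.** Choose one outcome and make the three sections agree, before outcome data are analysed.

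**Option A, keeping BMI primary.** Under Data analysis, make BMI the outcome of the 3-month model and the maintenance-phase model, with baseline BMI in place of baseline weight and gender retained. State that the Hochberg rule at 2.5% per time point applies to BMI. Report weight as a secondary outcome from the same models at the 5% level. This costs only wording, since height and weight are already measured and the sample size is already in BMI units.

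**Option B, making weight primary.** Change the primary outcome in the abstract to weight, restate the planned difference and SD under Sample size in kg with their basis, and state that the Hochberg rule applies to weight. This needs a target difference and SD in kg that the document does not now give.

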#### Phase 1 - Weight-loss interventions

Participants were initially randomized to one of three groups:

(1) Group 1, wait-list control; subsequently re-randomized to Group 2 or 3 after an initial 12-week control period;

(2) Group 2 followed the standard (Basic) commercial online weight loss program;

(3) Group 3 followed an extra support (Enhanced) version of the online weight loss program and received system-generated personalized feedback, based on diary entries and website use.

At the end of the initial 12 weeks of weight loss, those in Groups 2 and 3 could choose to undertake a further 12 weeks of weight loss or if they had achieved their goal weight, which was a loss of a minimum of 10% of initial body weight, they were re-randomized to one of two maintenance of lost weight programs (Phase 2).

#### Phase 2

Maintenance Group 1 (M1) was usual care whereas Maintenance Group 2 (M2) was enhanced support. Phase 2 will run for 12 months for those commencing after 6 months of weight loss or for 15 months for those entering after only 12 weeks of weight loss.

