### Outcome measures

Assessments were at baseline, 3, 6 and 18 months. The Phase 1, Group 1 control participants received an extra assessment at the end of the initial waiting list control period and were then also evaluated at 3, 6 and 18 months from the start of weight loss, meaning they will participate for a total of 21 months.

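### The maintenance model has one group coefficient and no group-by-time term, so if several visits enter it does not estimate the 18-month M1 v M2 difference that the primary test needs

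*Protocol article*

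**What the plan says.** The maintenance comparison is specified term by term in the Data analysis section. The outcome is each participant's weight at the post-treatment assessments, in the plural and with no visits named. For predictors, "the main predictor of interest will be treatment group and baseline weight will be included as a covariate". The list then closes: "Other independent variables included in the model will be: time, gender, kilojoule intake at baseline and physical activity at baseline". No group-by-time term and no 18-month contrast appear. The next paragraph fixes when the primary tests are made: "Statistical significance of the primary efficacy analysis (at three months and 18 months"), with a family-wise error of 2.5% at each time point.

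The schedule is given under Outcome measures: "Assessments were at baseline, 3, 6 and 18 months". The Randomization section says that M1/M2 are assigned at the end of the weight-loss phase. The Phase 2 text shows that this happens at one of two times: "Phase 2 will run for 12 months for those commencing after 6 months of weight loss or for 15 months" for those who enter after only 12 weeks. In the Outcome measures and Timelines for Programs sections, baseline means the assessment at study entry.

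**The concern.** A single group coefficient with time as a main effect assumes that M1 and M2 differ by the same amount at every visit in the model. That cannot be true of any visit at or before the maintenance randomisation, where the true difference is zero. It is unlikely between a visit three months after randomisation and one 12 to 15 months after. The 3-month model in the same section avoids the problem because its outcome is tied to one visit. The maintenance model is not tied to 18 months, although one of the two primary tests is.

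At stake is what the second primary test estimates. If M1 and M2 never differ, the coefficient is zero and the test remains valid. If a difference develops by 18 months, the estimate is pulled toward zero and power falls.

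A second, smaller matter is the covariate. The natural baseline for M1 v M2 is weight at the maintenance randomisation. It is measured at the 3- or 6-month visit, but the model adjusts for study entry.

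**Working it through.** **The plan's own figure.** Inputs from the Sample size section: power 90%, BMI difference Δ = 1.5 kg/m², SD = 1.5, alpha 0.05 on two sides. The result stated there: "a sample size of 48 participants (24 males and 24 females) is needed for each maintenance group at 18 months".

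n per group = 2 × SD² × (1.960 + 1.282)² / Δ² = 2 × 10.51 × (1.5/1.5)² = 21.0, so 22; the exact t-test gives 22.02, so 23. This agrees with 24 per sex if 90% power is meant within each sex. With the sexes pooled, 48 per group gives 99.8% power at 0.05 and 99.6% at 0.025. I use 1.5 kg/m² as the true 18-month difference. The ratios below do not depend on the unit.

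**What the written coefficient estimates.** With categorical time and balanced visits, the large-sample group coefficient is 1′V⁻¹d / 1′V⁻¹1, where d holds the true group difference at each visit and V is the visit covariance. Under exchangeable covariance (a random intercept) the weights are equal, whatever the correlation.

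- Visits 3, 6 and 18, no difference before 18: (0 + 0 + 1.5)/3 = 0.50, ratio 0.33.
- Visits 6 and 18, no difference at 6: (0 + 1.5)/2 = 0.75, ratio 0.50.
- Visits after each person's re-randomisation only: 3-month entrants (share p) contribute 6 and 18 months, the others 18 only. With f the 6-month difference as a fraction of the 18-month one and ρ the visit correlation, ratio = [p(1+f)/(1+ρ) + (1−p)] / [2p/(1+ρ) + (1−p)].
- 18 months only: ratio 1.0.

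The share p is not in the document. I assume 10% to 50%, f = 0.3/1.5 = 0.2, and random-intercept and residual SDs of 1.2 and 0.9, so ρ = 1.44/2.25 = 0.64. For p = 0.1 the third ratio is 0.973/1.022 = 0.95; for p = 0.5 it is 0.866/1.110 = 0.78. A random-intercept fit to 4,000 simulated participants with the same inputs gave 0.96 and 0.82. The simulation error of such a ratio is about (1.5 × 2/√4000)/1.5 = 0.03, so the two agree. The simulation gave 0.35 to 0.36 for all three visits, and 0.46 to 0.50 for the re-randomisation visit plus later visits.

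**Power**, for illustration, with SD held at 1.5 and 48 per group: SE = 1.5 × √(2/48) = 0.306; power = Φ(difference/0.306 − z), with z = 1.960 or 2.241.

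| Visits in the outcome | Ratio | 1.5 becomes | Power at 0.05 / 0.025 |
|---|---|---|---|
| 3, 6, 18 | 0.33 | 0.50 | 37% / 27% |
| 6, 18 | 0.50 | 0.75 | 69% / 58% |
| After re-randomisation only | 0.82 to 0.96 | 1.23 to 1.44 | at 1.23: 98% / 96% |
| 18 only | 1.0 | 1.50 | 99.8% / 99.6% |

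The covariance matters too. With three visits and a correlation decaying at 0.95 to 0.98 per month, the ratio is 0.47 to 0.49. With variance growing in proportion to time, as in a random walk, all the weight falls on the earliest visit and the ratio is 0.

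**The baseline covariate.** Assume independent BMI changes with SD 1.2 (0 to 3 months), 0.8 (3 to 6) and 1.5 (6 to 18). Adjusting 18-month BMI for entry BMI leaves a residual SD of √(1.44 + 0.64 + 2.25) = 2.08, and SE = 2.08 × √(2/48) = 0.42 (0.43 in simulation). Adjusting for BMI at re-randomisation leaves 1.5, SE 0.31. Both analyses estimate 1.5 without bias. If the SD of change over the whole weight-loss phase is instead 0.5, 1.0 or 2.0, the entry-adjusted SE is 0.32, 0.37 or 0.51, against 0.31.

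**The case against.** The strongest reply is that the text nowhere says that visits before the M1/M2 randomisation are outcomes. A weight taken before a treatment starts is not naturally a post-treatment weight. Those who enter after 12 weeks have both 6 and 18 months afterwards, which is enough to explain the plural and the time term. The article also names 18 months as a primary time point, so an 18-month contrast may be intended and spelled out in a fuller analysis plan.

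Much of this stands. A reader might infer that the model as written cuts the effect to a third and power to below 30%. The document does not support that. It requires the 3- and 6-month weights to be outcomes for everyone, no M1/M2 difference at either visit, and exchangeable covariance. On the mildest multi-visit reading the loss is modest.

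Two things do not fall to this reply. The article does not merely omit detail: it lists the model terms, and that list holds one group coefficient. And the 6-and-18 reading has some support, because Timelines for Programs places the wait-list group's post-intervention assessments at 9 and 21 months, that is 6 and 18 months after they start the program.

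A reader might also infer that the study-entry baseline biases or dilutes the comparison. It does not. M1 and M2 are randomised, so the choice of baseline affects only precision. The same holds for leaving out Phase 1 arm and entry route.

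**Conclusion.** The point holds in a limited form. The listed model does not target the 18-month M1 v M2 difference unless 18 months is the only visit in it, and then the time term has no function. If several visits enter, a difference that emerges by 18 months is understated. The ratio is about 0.33, 0.5, or 0.82 to 0.96, according to which visits are meant; the document does not settle this. The first two figures assume exchangeable covariance and no difference at the earlier visits. The last also rests on an assumed 10% to 50% entering at 3 months and a small 6-month effect in them.

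The baseline covariate is a separate question of efficiency. That baseline means study entry here is inferred from usage elsewhere in the article. The fall in SE from 0.43 to 0.31 rests wholly on assumed change SDs, and the gain could be small.

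**What to change.** Make the 18-month primary analysis a regression of BMI at 18 months on M1/M2, adjusted for BMI at the maintenance randomisation and gender. Phase 1 arm and entry route (12 or 24 weeks) are optional further covariates for precision. BMI is named here because the Abstract declares it the primary outcome and the sample size is stated in it, whereas the Data analysis section models weight.

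If the mixed model is kept, name the outcome visits and admit only those after each participant's maintenance randomisation, add group-by-time, and state that the 18-month contrast is the primary test.

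The cost is a change of analysis wording before the data are analysed. The 3-, 6- and 18-month measurements are already in the schedule, so no new data are needed.
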